### Evaluation Framework Overview

**Question**: Is the use of LMWH as compared to UFH cost-effective for the prevention of VTE in critically ill medical-surgical patients?**Perspective**: Our primary perspective is the acute healthcare system perspective. We will perform sensitivity analyses from various geographic regions participating in the PROTECT trial.**Clinical outcomes**: Rates of all thromboses, DVT, PE and complications (for example, bleeding and HIT), length of stay and mortality (ICU and hospital).**Costs**: All direct and indirect medical costs associated with treatment and complications (such as ICU and non-ICU hospitalization, personnel, medications, diagnostic testing and procedures) will be identified and evaluated. Costs will be converted to Canadian and United States (2013 dollar rates) costs.**Evaluation**: Our primary outcome is the incremental cost per in-hospital thrombotic event avoided. Long-term results will be presented in terms of costs per life year and quality-adjusted life years gained, using utilities from studies of appropriate duration, to allow for broad comparison of cost-efficacy with other medical interventions.**Comparators**: We will compare LMWH with UFH for outcomes and associated costs.**Time horizon**: We will focus on near-term horizons; costs and incremental cost effectiveness ratio outcomes at ICU and hospital discharge. We will model long-term outcomes over a lifetime horizon.**Discounting**: We will discount cost and utilities at 3% for any longer-term (over one year) analyses.**Uncertainty**: We will use sensitivity analyses and bootstrapping to produce confidence intervals.

DVT = deep vein thrombosis; HIT = heparin induced thrombocytopenia; ICER = incremental cost-effectiveness ratio; ICU = intensive care unit; LMWH = low molecular weight heparin; PE = pulmonary embolism; UFH = unfractionated heparin; VTE = venous thromboembolism.

### Outcomes Overview

**Primary outcome**:Incremental cost per thromboses (any site) avoided**Secondary outcomes**:(i.)Incremental cost per PE avoided(ii.)Incremental cost per DVT avoided(iii.)Incremental cost per major bleeding event avoided(iv.)Incremental cost per episode of HIT avoided**Tertiary outcomes**:Incremental cost per life year and quality-adjusted life year gained (lifetime horizon)

### E-PROTECT subgroups

As subgroup analyses, we will investigate specific patients in the PROTECT trial who may have differential effects and costs as compared to the entire population, including patients with higher and lower severity of illness (APACHE^1^ II score ≥25 versus <25), patients with a body mass index of ≥40 kg/m^2^ versus <40 kg/m^2^, patients requiring inotropes or vasopressors at enrollment versus those who do not and medical versus surgical patients. Although ventilation status was initially planned as a subgroup, approximately 90% of patients were mechanically ventilated at enrollment [7] and thus analysis in this subgroup will not be informative. We will directly calculate the incremental cost difference and generate 95% confidence intervals using the bias corrected and accelerated (BCa) method in R, among 1,000 bootstrap samples. We will examine the relative influence of all individual costs using a Tornado diagram.

### E-PROTECT sensitivity analyses

As patient characteristics, effects and costs may differ outside of tightly controlled clinical trials and in various jurisdictions, we plan a number of sensitivity analyses to explore how incremental cost-effectiveness ratios may change with plausible differences in values, including costs of LMWH and UFH, and per day cost of care in ICU and hospital wards. We will also perform sensitivity analyses using the efficacy analysis of the PROTECT trial that considered only patients who received the study drug for two days or more and had two or more leg compression ultrasounds, and by considering only symptomatic thromboses. Multi-way sensitivity analyses will be performed by varying the estimates of pairs of potentially influential variables. We will perform a probabilistic sensitivity analysis of pairs of known costs and effects from the PROTECT trial, using bootstrapping techniques, among 1,000 samples, with replacement, in order to generate an incremental cost-effectiveness plot [26, 27].

### Secondary analyses

#### E-PROTECT post-hospital discharge modeling

Some clinical events may occur after ICU and hospital discharge and these events may utilize resources (such as re-admission to the ICU, rehabilitation and physician visits). Because we cannot follow all patients in the PROTECT trial over their actual life expectancy, we may use discharge vital statistics and known post-critical illness follow-up literature to model the lifetime effects and cost-efficacy ratios of prevention strategies for all patients in the PROTECT trial, depending upon the results for the in-hospital time horizon. We will know clinical events and outcomes until death or discharge from hospital. However, if the primary analysis implies that long-term effects and costs are important to explore (particularly if the primary analysis demonstrates one strategy is more costly but with greater effects), post-discharge, a Markov-based process (Figure 1) will be used to model longer-term events and will allow patients to transition between states of health or illness until all patients in the model have died [5].

**Figure 1 Fig1:**
[figure not shown]
**Markov model for long**-**term outcomes and costs of critically ill patients in E-**
**PROTECT.** See Sud *et al*. [5]. ICU = intensive care unit; LMWH = low molecular weight heparin; LTC = long-term care; M = Markov node; UFH = unfractionated heparin; VTE = venous thromboembolism.

Both background mortality and increased mortality due to the initial illness, thrombosis event or complication will be considered. The cycle length will be one month. Transition probabilities will be taken from the E-PROTECT follow-up cohort and literature of post-ICU survival. The E-PROTECT long-term model is informed by the structures of published models for prophylaxis with LMWH in other populations [5] and the actual course of the patients in the PROTECT trial. We will combine these data, and known utilities of post-ICU discharge states, with outcomes and life years determined by the PROTECT trial and the long-term model in order to derive a measure of quality-adjusted life years and associated incremental cost-efficacy ratios. Given our in-hospital primary time horizon and focus on thrombotic events in the PROTECT trial, we intentionally will not directly measure short-term health-related quality of life measurements for our primary time horizon, but will apply measures of health-related quality of life for modeled post-hospital survival using data from longitudinal studies of critically ill patients over an appropriate time horizon [28–36]. We will apply 3% discounting for all effects and costs for any lifetime modeled events.

### Statistical analyses

All primary analyses will be based on the intention-to-treat principle, as per the primary analyses for the PROTECT trial. We use descriptive analyses to describe the baseline characteristics. Means (and standard deviations) or medians (and interquartile ranges) will be used to describe average effect and cost estimates, and Chi-square tests and two-sample t-test comparisons will be used as appropriate. We will test for differences in costs using standard non-parametric tests, and use nonparametric analysis of variance techniques to test for interactions with the heparin strategies. For missing or unavailable data, we will use imputation of the median value from the appropriate subgroups in E-PROTECT and compare results obtained with and without imputation to ensure large variations do not exist [37, 38]. Statistical significance for differences among *a priori* comparisons will be set at a P value of 0.05. Primary analysis will be undertaken using Excel (Microsoft Corp, Redmond Washington, United States), R (Free Software Foundation) and SAS (Cary, North Carolina, United States). Post-hospital discharge models will be constructed using Excel and TreeAge software (TreeAge Software Inc., Williamstown, Massachusetts, United States).

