## Methods/Design

### E-PROTECT background studies and methodologies

#### The PROTECT trial

The objective of the Canadian Institutes of Health Research (CIHR)-funded PROTECT trial [7, 8] was to evaluate LMWH versus UFH on the primary outcome of the incidence of proximal leg DVT diagnosed by compression ultrasound, with secondary outcomes of PE, venous thrombosis at any site, bleeding and heparin-induced thrombocytopenia (HIT). The study design was a randomized, stratified, concealed double-blind multicenter trial with enrolment throughout Canada, Australia, the United States, Saudi Arabia, the United Kingdom and Brazil. The PROTECT trial enrolled 3,746 critically ill patients between May 2006 and June 2010 according to previously published eligibility criteria [7, 8]. A central computerized web-based or phone-in randomization system ensured concealed randomization of patients to either dalteparin 5,000 international units (IU) daily or UFH 5,000 IU twice daily subcutaneously for the ICU stay. Only the research pharmacist at each participating centre was aware of the allocation. Bilateral proximal leg compression ultrasounds were performed within 48 hours of ICU admission, twice weekly and on DVT suspicion. A predefined algorithm was used to diagnose PE; bleeding, HIT, other thrombosis and complications were identified using *a priori* definitions and procedures. The PROTECT publication itself provides complete study data [7].

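### The main cost comparison ignores the stratified randomisation and the recorded baseline severity, so its intervals may be wider than they need be

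*Protocol article*

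**What the plan says.** **Design.** The PROTECT trial section states: "The study design was a randomized, stratified, concealed double-blind multicenter trial". The article does not name the stratification factors. On size: "The PROTECT trial enrolled 3,746 critically ill patients between May 2006 and June 2010".

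**Baseline variables.** The E-PROTECT subgroups section splits patients by APACHE II ("score ≥25 versus <25"), by body mass index at 40 kg/m², and then into "patients requiring inotropes or vasopressors at enrollment versus those who do not and medical versus surgical patients".

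**Main contrast.** The E-PROTECT analytic plan takes incremental cost as the difference between arms in median cost per patient, with means also reported. Incremental effect is the difference in event rates. Neither is adjusted.

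**Tests.** The Statistical analyses section says "Chi-square tests and two-sample t-test comparisons will be used as appropriate", and for cost: "We will test for differences in costs using standard non-parametric tests". Its only modelling step is to "use nonparametric analysis of variance techniques to test for interactions with the heparin strategies", which concerns interactions and not the main effect.

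**Intervals.** The subgroups section plans BCa intervals for the cost difference from 1,000 bootstrap samples. The sensitivity section plans a probabilistic analysis of cost-effect pairs "using bootstrapping techniques, among 1,000 samples, with replacement, in order to generate an incremental cost-effectiveness plot". Neither mentions strata or covariates.

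**A remark pointing the other way.** The Discussion, where it weighs the drawbacks of trial-based evaluation, says that estimates will be exposed to adjustments for case mix and severity. It gives no method.

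**The concern.** There are two separate mechanisms.

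- **Ignoring strata.** Stratified randomisation balances the arms on the strata. If the strata predict cost, the estimate varies less than an unstratified interval assumes, so that interval is conservative.
- **Ignoring baseline severity.** Variation in cost that baseline covariates could explain stays in the error term. The interval remains valid, but precision is lost.

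Both could matter for cost. Total cost is built from resource use and length of stay, with ward days, later ICU days and the first ICU day weighted 1 : 2.5 : 4. The base case applies common multi-country median prices, so differences between patients come from resource use, which severity and case mix may predict.

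The cost interval also carries weight. If LMWH is cheaper, the analytic plan reports a cost-minimisation analysis with the cost difference and its 95% confidence interval. The decision to model long-term outcomes depends on the primary result as well.

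**Working it through.** The article gives no standard deviation, explained variance, event rate or interval width, so there is no figure of its own to reproduce. What follows shows how large the effect could be.

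**Inputs.** N = 3,746 (The PROTECT trial section). Equal arms and a two-sided 95% level are assumed. R² is the share of cost variance explained by strata and baseline covariates; it is assumed over a range.

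**Step 1: crude interval for a mean cost difference.** Half-width = 1.96 × 2/√3,746 = 0.064 SD.

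**Step 2: gain from adjustment.** Adjusted width / crude width = √(1 − R²). Extra patients giving the same gain = 3,746 × [1/(1 − R²) − 1]. If stratification fully balances the explained part, the crude 95% interval actually covers with probability 2Φ(1.96/√(1 − R²)) − 1.

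| R² (assumed) | Width ratio | Narrower by | Equivalent patients | Coverage of crude interval |
|---|---|---|---|---|
| 0 | 1.000 | 0% | 0 | 95.0% |
| 0.05 | 0.975 | 2.5% | 197 | 95.6% |
| 0.10 | 0.949 | 5.1% | 416 | 96.1% |
| 0.20 | 0.894 | 10.6% | 936 | 97.2% |
| 0.30 | 0.837 | 16.3% | 1,605 | 98.1% |

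The coverage column applies only to the part explained by the strata. Leaving out a covariate that was not used to stratify does not raise coverage in this way.

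**Step 3: skewed costs, means and medians.** The simulation ran 300 trials per setting, with 3,720 patients in 20 blocked strata (assumed), log-normal costs (log SD 0.9) and an unstratified bootstrap within arm. It used a normal interval, not BCa.

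- With strata explaining about 22% of cost variance, the bootstrap SE for the mean difference was 0.0547 against a true 0.0491, a ratio of 1.11. For the median difference it was 0.0377 against 0.0327, a ratio of 1.15.
- With 4% to 7% explained, the ratios were 1.02 to 1.07 for means and 0.97 to 1.03 for medians. Simulation error on each ratio is about 4% (1/√(2 × 299)), so no excess is demonstrated for medians at this level.

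**Step 4: event rates.** Take two equal strata with average risk p and risk ratio r, so p₀ = 2p/(1 + r), p₁ = r·p₀ and R² = [(p₁ − p₀)²/4]/[p(1 − p)]. For p = 0.10 and r = 2: p₀ = 0.0667, p₁ = 0.1333, R² = 0.00111/0.09 = 0.012, narrowing 0.6%. For p = 0.02 and r = 2: R² = 0.002, narrowing 0.1%. These rates and ratios are assumed.

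**The case against.** The best defence is that an unadjusted comparison of 3,746 randomised patients is valid, that adjustment is an optional gain of unknown size, and that an article may leave covariate lists and resampling detail to a fuller plan. Much of this stands, and it limits the point in five ways.

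- A reader might infer that the intervals are certainly too wide. The article does not support that: it names no strata and gives no R², and at R² = 0 nothing is lost. Common unit prices also remove site price differences that strata might otherwise have explained.
- A reader might infer that the bootstrap ignores strata. The article neither says so nor excludes it.
- A reader might extend the point to thrombosis rates, where Step 4 shows almost nothing to gain.
- The base-case incremental cost is a difference in medians. The R² formula and a regression on cost both concern means, so they do not carry over directly.
- The article does not say that the baseline variables are complete for every patient, and it plans imputation for missing data.

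Two parts of the defence fail. The crude difference and the tests are stated choices, not omissions. The Discussion's remark does not supply the adjustment either: it concerns generalisability, and the only analyses described that match it are the subgroups.

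**Conclusion.** The point holds as one of efficiency, limited to cost. The plan describes crude cost comparisons although the trial was stratified and prognostic baseline variables are held. For the mean cost difference, about 2.5%, 5% and 11% of interval width could be saved at assumed R² of 0.05, 0.10 and 0.20. For the median difference, an unstratified bootstrap was clearly conservative only where strata explained about a fifth of cost variance.

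It might be tempting to read this as bias, as inflated type I error, or as chance imbalance corrupting the primary ratio. None of these follows. Randomisation keeps the crude contrast unbiased, its interval already allows for chance imbalance, and where strata are ignored the error is on the conservative side. The change is worth making because it is cheap, not because the planned result would be wrong.

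**What to change.** 1. Name the randomisation strata in the analysis plan.
2. Estimate the incremental mean cost, which is already to be reported, from a regression on arm, randomisation strata, continuous APACHE II, body mass index, vasopressor or inotrope use and medical or surgical status. State that this targets the mean and does not adjust the median difference.
3. Resample cost-effect pairs by arm within randomisation strata and refit the model in each resample. The same resampling serves the median difference. Merge very small cells first, because resampling within them understates variance. If hospital is a stratum, the average is 3,746/67 ≈ 56 patients per hospital, or about 28 per arm.
4. Keep the crude estimates as a sensitivity analysis. Event rates can stay unadjusted with little loss.
5. Reconcile the Discussion's statement on case-mix and severity adjustment with the analytic plan and the Statistical analyses section, either by pointing to the adjusted analysis or by saying that subgroups are meant.

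The cost is some plan wording and a few lines of R. No new data collection appears necessary, provided the baseline variables are reasonably complete. Trial status says costing was unfinished and allows further analyses with justification, so the covariates can still be fixed before costs are compared by arm.

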### E-PROTECT analytic plan

The base case cost-efficacy ratio is the ratio of incremental costs per incremental effects of LMWH versus unfractionated heparin during the period of hospitalization. Incremental costs will be derived for all patients by first calculating total costs for all patients in each arm of the PROTECT trial. Item costs will be multiplied by the frequency or event rates for medications administered, laboratory and radiological tests incurred, other diagnostic or therapeutic procedures performed, transfusions received, per day personnel and ICU or ward costs, depending upon number of events and length of stay in the ICU and hospital. Total, then median and mean per patient costs for each of the LMWH and unfractionated heparin groups will be calculated. Incremental costs will be taken as the difference in median per patient costs between groups; however, mean costs will also be provided in order to generate total costs. Effects for the base case analysis will be calculated separately for each primary (all thromboses), secondary (PE, DVT, major bleeding and HIT) and tertiary (survival) endpoints. Incremental effects will be taken as the difference in per patient event rates between groups. Therefore cost-effectiveness ratios will be displayed in terms of incremental costs divided by incremental effects, specifically, the cost to prevent a thrombosis at any site, the cost to prevent a PE, DVT, major bleeding event and episode of HIT, and life-year gained as is commonly used in cost-effectiveness analysis for VTE prevention strategies (Box 2) [6]. If costs are less in the LMWH group, a cost-minimization analysis will be reported, highlighting the difference in costs (with 95% confidence intervals) between groups.

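### The planned non-parametric cost tests and nonparametric ANOVA, read as rank methods, do not test mean cost per patient and need not agree with the planned bootstrap intervals

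*Protocol article*

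**What the plan says.** Three places in the protocol article bear on how a cost difference is estimated and tested.

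- **Statistical analyses.** A general sentence on describing effects and costs ends: "Chi-square tests and two-sample t-test comparisons will be used as appropriate". The next sentence deals with costs specifically: "We will test for differences in costs using standard non-parametric tests, and use nonparametric analysis of variance techniques to test for interactions". The interactions are those with the heparin strategies. The threshold follows: "Statistical significance for differences among *a priori* comparisons will be set at a P value of 0.05".
- **E-PROTECT analytic plan.** The contrast is defined as follows: "Incremental costs will be taken as the difference in median per patient costs between groups; however, mean costs will also be provided". The stated purpose of the means is to generate total costs. If LMWH costs less, a cost-minimization analysis is reported, "highlighting the difference in costs (with 95% confidence intervals) between groups".
- **E-PROTECT subgroups.** For APACHE II score, body mass index, inotrope or vasopressor use, and medical versus surgical status: "We will directly calculate the incremental cost difference and generate 95% confidence intervals". The method is BCa with 1,000 bootstrap samples.

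No test is named beyond these descriptions.

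**The concern.** The stated objective is total cost and incremental cost-effectiveness from the acute healthcare system's perspective. Only the mean cost per patient, multiplied by the number of patients, gives a total. A rank test asks whether a patient in one arm tends to cost more than a patient in the other. With skewed costs the answer can differ from the comparison of means in either direction.

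It is not in general a test of medians either. Two distributions can share a median while one lies above the other in both tails.

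The plan thus holds three quantities side by side: a rank comparison for the P value, a median difference for the ratio and (by the article's definition) the interval, and a mean for total cost. Nothing says which governs if they disagree.

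An interaction on ranks raises a further problem. A fixed dollar effect is a larger proportional change where costs are low, so it moves ranks more there. An effect that is constant in dollars can then look like effect modification. At stake are reported statements that costs differ, or that LMWH is more economical in one kind of patient.

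**Working it through.** The article gives no power, error rate or cost distribution for these tests, so there is no stated figure to reproduce. The check is by simulation.

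**Inputs from the article:** 3,746 patients; P value threshold 0.05.

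**Assumptions:** equal split, 3,746 / 2 = 1,873 per arm; two-sided tests; lognormal costs; Wilcoxon-Mann-Whitney as the rank test; ANOVA on rank-transformed costs as the interaction test. There were 1,000 runs per setting, so the Monte Carlo standard error near 5% is √(0.05 × 0.95 / 1,000) = 0.7 percentage points.

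**A. Equal means.** Mean $40,000 in both arms, log-SD 1.0 in one. A lognormal with mean m and log-SD s has median m·exp(−s²/2), so the reference median is 40,000 × exp(−0.5) = $24,261.

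| log-SD, other arm | its median | median difference | rank test rejects | Welch t-test rejects |
|---|---|---|---|---|
| 1.00 | $24,261 | 0 | 5.3% | 5.7% |
| 1.05 | $23,049 | −$1,212 | 30.9% | 4.8% |
| 1.10 | $21,843 | −$2,418 | 85.8% | 5.1% |
| 1.20 | $19,470 | −$4,791 | 100% | 6.6% |

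A hand check agrees. With equal means the log-means differ by (s₂² − s₁²)/2. The probability that a patient in one arm costs more than one in the other is Φ of that difference over √(s₁² + s₂²). The rank statistic's standard error is about √((2/1,873)/12) = 0.00943.

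- Log-SD 1.05: (1.1025 − 1)/2 = 0.05125; 0.05125/√2.1025 = 0.0353; Φ = 0.5141; z = 0.0141/0.00943 = 1.49; power ≈ Φ(1.49 − 1.96) = 32%.
- Log-SD 1.10: 0.105/√2.21 = 0.0706; Φ = 0.5282; z = 2.98; power ≈ Φ(1.02) = 85%.

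**B. Equal medians, unequal means.** Log-mean 10 in both arms, log-SD 1.0 versus 1.2. The means are exp(10.5) = $36,316 and exp(10.72) = $45,252, a gap of $8,936 or 25%. The rank test rejects in 5.1% of runs, Welch in 98.7%.

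**C. Same dollar effect in two subgroups.** Two equal subgroups with means $30,000 and $60,000, log-SD 1.0, and the same amount added to every treated patient's cost.

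| effect in each subgroup | rank interaction rejects | mean-scale interaction rejects |
|---|---|---|
| $0 | 4.3% | 4.2% |
| $2,000 | 8.9% | 5.7% |
| $4,000 | 18.5% | 5.1% |
| $6,000 | 30.6% | 4.9% |

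The reason shows in the proportions: $4,000 is 13% of $30,000 but 7% of $60,000.

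**Other assumed values.** With mean $60,000 and log-SD 0.85 versus 0.95, the rank test rejects in about 84% of runs and a mean-based test in about 5%. With a subgroup cost ratio of 2.5 and a $5,000 effect in both, the rank interaction rejects in about 25% and the mean-scale test in 6%; at $2,500 the figures are 10% and 6%.

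**The case against.** **The plan's contrast is the median.** A reader might infer from table A that the plan's type I error is 31% or 86%. The documents do not support that. Incremental cost is defined as a median difference, and in those rows the medians really differ. Lognormal costs are symmetric on the log scale, so under this model the rank test's null coincides with equal medians; setting B shows it holding about 5% there. The rates are errors only against a null of equal means. This stands, and it means the remedy must start with the definition of incremental cost.

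**The interaction result is conditional.** It needs a non-zero effect of treatment on cost and unequal subgroup cost levels. This stands too: at zero effect the test held 4.3%.

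**The methods are not named.** A permutation or bootstrap test of means is also non-parametric, the t-test sentence could be read to cover costs, and the interactions are not expressly tied to the listed subgroups. This weakens the point only a little. The sentence specific to costs follows the t-test sentence and overrides it. Beside nonparametric analysis of variance, rank methods are the natural reading, and the subgroups are the natural place for interactions.

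**Conclusions do not rest on P values alone.** Intervals and a bootstrap cost-effectiveness plot are planned, and the primary outcome is a ratio. This is true and limits the harm, but a P value on another hypothesis would still be reported beside them.

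**Stratification.** Since "The study design was a randomized, stratified, concealed double-blind multicenter trial", a reader might add that the analysis wrongly ignores the strata. The article does not list them, a condensed article may be silent on adjustment, and the Discussion mentions adjustment for case-mix and severity. That is no finding.

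**Conclusion.** The point holds in a limited form. The cost and interaction tests, read in the ordinary way, do not address mean cost, and in general they do not address the median difference either. P value, interval and total cost can therefore tell different stories. The mismatch follows from the methods chosen. Its size depends on the assumed lognormal costs, equal allocation and test forms, none of which the article gives.

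Under those assumptions a rank test can be significant in most runs when mean costs are identical. It can also stay at its nominal level when they differ by a quarter. The spurious interaction runs from about 9% to 31% for common effects of $2,000 to $6,000. The change should be made. It does not show that the in-hospital ratios or their intervals are invalid on the article's own median definition.

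**What to change.** 1. In the E-PROTECT analytic plan, take incremental cost as the difference in arithmetic mean cost per patient. Without this step, a test of means would sit beside a ratio built on medians.
2. In Statistical analyses, test that difference with the bootstrap already planned. Test interactions as the bootstrap difference-in-differences in mean cost between subgroups. State that estimate, interval and P value all refer to this quantity.
3. Keep medians, interquartile ranges and any rank tests as descriptive.

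The cost is a few sentences and a small extension of bootstrap code already needed. The Trial status section says that costing was incomplete at submission and that further analyses may be reported with justification, so the change can be made and should be dated before costs are compared by arm. The real downside is precision: with skewed costs, mean differences have wider intervals. A net-benefit interaction is not required, since the Discussion says there is no clear cost threshold for an avoided VTE event.
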